**Fig. 4 Fig4:**
[figure not shown]
Schematic overview of the tasks in the decision-making battery. **a** Delay discounting task. **b** Probability discounting for gains. **c** Probability discounting for losses. **d** Mixed gambles task [66]

### Stress induction

Stress is induced with the Trier Social Stress Test (TSST) [98] as one of the most frequently inserted research tools for the induction of acute psychosocial stress in experimental, laboratory research worldwide. The TSST is a standardized laboratory protocol, which provides a reliable and ecologically valid stressor [98]. The TSST contains elements of social evaluative threat and uncontrollability, which are associated with high cortisol responses [99]. The test is divided in three equal five-minute parts. It begins with a preparation period, followed by a free speech for a job interview and finishes with an arithmetic task. All tasks are held in front of a two-person audience. The TSST leads to robust changes in the hypothalamus–pituitary–adrenal (HPA) axis and the autonomic stress response compared to other stress induction paradigms [39, 100].

In the control condition, subjects participate in a Placebo-TSST, which is comparable in time and task division but without any audience and stress exposure for the participants [101]. It starts with a preparation period, followed by a free speech about the last vacation and finishes with a simple task of counting forward. Furthermore, participants are standing during the two tasks. This creates a setting that is as close as possible to the TSST, but does not contain stressful components (evaluative threat and uncontrollability).

### Ad-libitum taste test

After completion of the behavioral tasks and the intervention, participants are asked to take part at an ad-libitum taste test as a covert measure for alcohol consumption. The ad-libitum taste test is a widely used method, which provides an unobtrusive and indirect measure of participants’ motivation to drink alcohol [84]. All participants are given two 0.33 l glasses of beer (two brands each containing 5% alcohol) and two 0.33 l glasses containing different soft drinks. Participants are instructed that they have 15 min to taste each glass to rate qualities about each drink (e.g. gassy, bitter). Participants are told to drink whatever amount necessary to make accurate judgements. The dependent variable is the amount of alcoholic beverage (beer) consumed and can range between 0 and 666 ml (equals 26.64 g ethanol). Non-alcoholic drinks are presented to control for the potential effect of thirst. The ad-libitum taste test is a valid method for the assessment of alcohol intake in the laboratory supported by strong associations between ad-libitum consumption and typical alcohol consumption [84]. It is also robust against several potential confounders such as time of day or participant awareness [84]. The taste test has been used to investigate a number of potential influences on alcohol consumption, including alcohol cues [102, 103, 104], impulse control [105, 106], and social influences [107], and it has been used to establish initial proof of concept for novel behavioral interventions [108, 109, 110].

### Procedure

The main assessments are conducted between 14–20 p.m. in order to reduce the variance in biological measures (e.g. saliva cortisol) due to diurnal rhythms [111]. It is also likely that the willingness to drink alcohol is smaller in the morning than in the evening while there is no influence of day time on alcohol consumption in the ad libitum taste test between 14p.m. and 20p.m. [84]. Figure 5 gives an overview of the main study procedure. First, participants are asked to provide written informed consent. Participants’ absence from alcohol is verified by taking a breathalyzer reading with any value above zero leading to the immediate end of the examination. Hair strands for basal cortisol secretion are taken scalp-near from a posterior vertex position to be able to reflect basal cortisol secretion within two months prior to the respective assessment point. Then participants complete the baseline questionnaires including the measures of the proposed moderators (childhood maltreatment, trait impulsivity) and variables that might affect the associations of interest (usual alcohol consumption, drinking motives, stressful life events, trait anxiety, difficulties in emotion regulation, psychological flexibility). Subsequently, participants either take part in the stress induction (experimental condition) or placebo intervention (control condition) followed by behavioral assessments. Deviating from previous TSST protocols, the stress condition is maintained during the behavioral assessments. Therefore, participants are instructed that the TSST panel remain observing and evaluating the given performance during the computer tasks and further the camera is still pointed on the participant. The ad libitum taste-test is the last assessment of the procedure. After the taste test, all participants are debriefed about the true study purposes including the TSST procedure. Moreover, repeated breathalyzer readings are taken until blood alcohol concentration reaches 0.0‰ in two consecutive measures. Participants willing to leave before blood alcohol concentration reaches 0.0‰ have to confirm that they do not drive when leaving the laboratory. Participants who insist to leave with a blood alcohol concentration still being higher than 0.4‰ (only expected in rare cases) are sent home with a taxi.

**Fig. 5 Fig5:**
[figure not shown]
Study procedure. *Note*: *IC* Informed consent, *TSST* Trier social stress test

### Sample storage, biochemical analyses and data preparation

The saliva samples are taken using salivette ‘code blue’ devices (Sarstedt, Nümbrecht, Germany) directly before the intervention and at three time points after the intervention (Fig. 5). Saliva samples are stored at − 20 °C in a laboratory freezer. After thawing, saliva samples will be centrifuged for 10 min at 4000 rpm. Salivary cortisol concentrations will be determined using a commercially available chemiluminescence assay (CLIA, IBL-Hamburg, Germany). Concentrations of salivary alpha-amylase will be detected by using an in-house enzyme kinetic method according to the protocol described in [63]. Hair cortisol concentrations will be determined via liquid chromatography tandem mass spectrometry (for detailed information on analysis methods see [56]).

Dimensional variables that are not normally distributed (expected e.g. for hair cortisol concentration, salivary cortisol and alpha amylase) will be Box–Cox transformed towards normal distribution. For all biological and behavioral variables, participants with outlying values of more than three standard deviations above the mean will be excluded from the respective analysis. Besides, robust linear regressions will complement conventional linear regressions because they down weight observations with large residuals to meet the assumption of equal variances of residuals. Composite measures of the entire cortisol secretion during the TSST (area under the curve with respect to ground; AUC_G_) and the cortisol stress reactivity (area under the curve with respect to increase; AUC_i_) will be calculated [112]. Analysis with these variables will be adjusted for initial cortisol concentration to alleviate confounding risk as AUC variables may be comprised of variance due to stress reactivity and stress-unrelated HPA axis activity [113]. All analysis including cortisol secretion during the TSST will be run twice with all participants in the first and with exclusion of non-responders to the TSST (increase of 1.5 nmol/l compared to baseline [114]) in the second run. With regard to alpha-amylase, both AUC measures and peak minus baseline levels will be calculated.

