#### Behavioral measures

In addition to self-report measures, three behavioral tasks are conducted to measure attentional bias to alcohol related stimuli, inhibitory control and impulsivity as possible mediators in the association between stress and alcohol use [18, 90]. Attentional bias towards alcohol-related cues is measured using a dot-probe task (Fig. 2), which was programmed based on previous tasks in similar settings [41, 90]. Subjects are presented with pairs of matched alcoholic (beer) and non-alcoholic beverages for 500 ms (stimulus-onset asynchrony, SOA). Another SOA of 100 ms will be added to the paradigm in the proposed study to be able to capture automatic initial reactions (see [91]). Stimuli were chosen based on expert ratings regarding similarity in color, shape and recognition. Subjects respond to a probe that appears behind either the alcoholic or the non-alcoholic beverage. The difference in reaction time between alcoholic and non-alcoholic stimuli is a measure of attentional bias towards alcohol-related cues. Although the dot-probe task is a widely used paradigm to measure attentional biases, there is debate about its reliability [92, 93]. A new trial-based conceptualization of attentional bias has been proposed, which can increase reliability [94].

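### A value-based, upper-tail 3 SD exclusion is applied to post-randomisation mediators, with scale and pooling left open and no stated analysis that keeps everyone

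*Protocol article*

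**What the plan says.** The rule is in the protocol article, section Sample storage, biochemical analyses and data preparation. Its scope is "For all biological and behavioral variables", and its content is that "participants with outlying values of more than three standard deviations above the mean will be excluded from the respective analysis". There is no lower-tail counterpart and no requirement that the value be an assay or procedural failure. The text does not say whether the mean and SD are taken over both arms or within each arm.

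Three neighbouring statements matter:

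- The sentence before the rule says that non-normal variables, with hair cortisol, salivary cortisol and alpha-amylase as examples, "will be Box–Cox transformed towards normal distribution". It does not say whether screening comes before or after this step.
- The sentence after it adds that "robust linear regressions will complement conventional linear regressions because they down weight observations with large residuals".
- Later in the same paragraph: "All analysis including cortisol secretion during the TSST will be run twice with all participants in the first and with exclusion of non-responders". The contrast there is with people who did not respond to the stressor, and it concerns cortisol only.

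Under Behavioral measures, "three behavioral tasks are conducted to measure attentional bias to alcohol related stimuli, inhibitory control and impulsivity". According to Procedure, these tasks follow the stress induction and are done while the stress condition is kept up. Statistical analyses uses the saliva markers and the tasks as mediators.

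**The concern.** The variables screened include responses to the randomised condition. The protocol article itself expects a response: "The TSST leads to robust changes in the hypothalamus–pituitary–adrenal (HPA) axis and the autonomic stress response". If one cut-off is computed over both arms, people above it on saliva cortisol or alpha-amylase will come mainly from the stress arm. Exclusion then depends on both assigned condition and response, so the comparison that remains is no longer the randomised one.

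What is at stake is the stress-to-mediator path. Mediation through endocrine and autonomic reactivity is an a priori hypothesis in both drinking strata, and a high reactor is the kind of participant that hypothesis is about. The outcome comparison within the mediation model uses the same reduced sample, so it is affected as well.

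**Working it through.** The plan gives no number of expected exclusions, so there is no figure of its own to reproduce.

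**Inputs.** From the protocol article: target 400, four groups of 100, hence 200 stress and 200 control; cut-off at mean + 3 SD. Assumed, because the article gives no distribution: lognormal cortisol, log-mean difference D = 0.5–0.7, log-SD s = 0.5–0.6.

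**1. Raw values, pooled cut-off.** With the control log-mean set to 0:

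- arm means m0 = exp(s²/2) and m1 = exp(D + s²/2); arm variances v = (exp(s²) − 1)·m²
- pooled SD = √[(v0 + v1)/2 + (m1 − m0)²/4]; cut-off c = (m0 + m1)/2 + 3·SD
- expected removals: stress 200·[1 − Φ((ln c − D)/s)], control 200·[1 − Φ(ln c/s)]
- mean of those kept, in an arm with log-mean μ: m·Φ((ln c − μ − s²)/s)/Φ((ln c − μ)/s)

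Example, D = 0.5 and s = 0.6: m0 = 1.197, m1 = 1.974, SD = 1.143, c = 1.586 + 3 × 1.143 ≈ 5.01, ln c = 1.612. The stress z is (1.612 − 0.5)/0.6 = 1.853, giving 6.38 removed. The control z is 1.612/0.6 = 2.687, giving 0.72 removed. The arm difference falls from 0.777 to 0.645, a loss of 17%.

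| D | s | Removed stress / control | Stress share | Arm difference, full → trimmed | Loss |
|---|---|---|---|---|---|
| 0.5 | 0.5 | 6.11 / 0.41 | 94% | 0.735 → 0.638 | 13% |
| 0.5 | 0.6 | 6.38 / 0.72 | 90% | 0.777 → 0.645 | 17% |
| 0.7 | 0.5 | 6.51 / 0.12 | 98% | 1.149 → 1.017 | 11% |
| 0.7 | 0.6 | 6.96 / 0.29 | 96% | 1.214 → 1.029 | 15% |

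Simulating 4,000 trials per row, with the cut-off estimated from the data, gives the same losses to within half a percentage point.

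**2. Raw values, arm-specific cut-offs.** The cut-off scales with the arm, so both arms lose the same number: 3.08 each at s = 0.5 and 3.43 each at s = 0.6. Both means shrink by the same factor, so the difference falls by 3.4% or 4.8%, whatever D is.

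**3. Transformed values, pooled cut-off.** On the log scale d = D/s and the cut-off is d/2 + 3·√(1 + d²/4). Expected removals over both arms are 0.31–0.49 of 400, and the arm difference falls by 0.4–0.8%.

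**4. Reactivity score.** AUCi was simulated from four samples (assumed baseline log-SD 0.4–0.5, mean log response 0.5–0.7 with SD 0.4–0.5, 2,000 replicates). A raw pooled cut-off removes 7.3–8.2, over 99% from the stress arm, and the difference falls by 10–15%. With arm-specific cut-offs about 5 are removed, about 70% from the stress arm, and the loss is 5–9%. With concentrations log-transformed first, about one or fewer is removed and the loss is about 1% or less.

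**5. Indirect effect, raw pooled cut-off.** Under the assumptions of step 1, trimming lowers the indirect effect by 11–17% if drinking is linear in raw cortisol. It raises it by 2–7% if drinking is linear in log cortisol, because the fitted mediator slope steepens. Over a wider grid with drinking linear in log cortisol (d = 0.8–1.5, log-SD 0.5–1.0, mediator slope 0.3, direct effect 0.1), the trimmed indirect effect is 0.99–1.39 times the full-sample value. The total effect in the trimmed sample is 0.94–0.96 times.

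**The case against.** The best defence is the order of the sentences: transformation is described first, so screening may be meant to follow it. On that reading the rule is almost inert. This stands, and it sets the lower end of the range. It does not settle the matter, because the order is not stated. Box–Cox also needs positive values, whereas AUCi and peak minus baseline can be negative. The text names no shift and does not say whether AUCs are built from raw or transformed concentrations.

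It can also be said that a pre-specified 3 SD screen with a robust companion analysis is ordinary practice, and that order and pooling belong in a fuller plan. The second part is fair. But the exclusion itself is stated here as a rule, and robust regression cannot down-weight people who have already been removed.

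Several stronger readings are tempting and are not supported:

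- *The cut-off is pooled.* The text says only the mean; pooling is an inference.
- *Indirect effects are understated.* Step 5 shows no fixed direction.
- *One-sidedness causes the loss.* On raw cortisol the mean minus 3 SD is below zero in all four rows (−1.2 to −2.4), so a two-sided raw rule would remove the same people. The raw scale and the pooled cut-off produce the loss.
- *Strong bias toward alcohol is trimmed and bias away from it is not.* The sign of the attentional bias score is not fixed, nor is that of the go/no-go score.
- *The primary outcome is trimmed.* "The dependent variable is the amount of alcoholic beverage (beer) consumed", but the taste test has its own section outside Behavioral measures and is listed as the outcome in Table 1. Whether the rule reaches it is unclear. If it did, the estimated effect would be about 1 ml of an assumed 50 ml.
- *Every covered variable is affected.* Hair cortisol reflects the two months before the visit, so exclusion on it cannot be a reaction to the stressor.

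**Conclusion.** The point holds in a limited form. The plan removes people on the observed value of post-randomisation mediators, in the upper tail only, and states no analysis that clearly keeps them. For saliva cortisol the consequence runs from negligible (about one person or fewer, about 1% or less, if transformation comes first) through a 3–5% loss (raw, arm-specific) to an 11–17% loss of the arm difference with 90–98% of exclusions from the stress arm (raw, pooled). These sizes rest on the assumed lognormal shape, D and s. The stress-arm imbalance further requires a pooled cut-off, or an arm with more skew as in AUCi. The same direction is expected for alpha-amylase, whose size was not worked out separately. For the three tasks the article gives neither the size of a stress effect nor, for two of the scores, a clear sign, so no stress-arm imbalance is claimed there. Indirect effects may be distorted in either direction. A confirmatory mediator result should not depend on unstated choices with that spread.

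**What to change.** Replace the sentence with a rule on these lines:

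- All valid observations stay in the main analyses.
- Only documented assay or technical failures are excluded, decided blind to condition.
- Influential points are handled by the planned transformation and by the planned robust regression, fitted to the full sample.
- If trimming is kept, it is a sensitivity analysis: two-sided, on the transformed scale or on residuals of the fitted model, with the order of steps and the reference group (pooled or per arm) stated.
- The trimming rule does not apply to taste-test beer volume.

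This changes a sentence or two and needs no new data. The price is somewhat larger residual variance in the conventional regressions.

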#### Biological measures

Hair strands are taken to reflect cumulative long-term cortisol secretion within two months prior to the respective assessment point [56]. The cumulative cortisol secretion consisting of basal cortisol secretion as well as stress-induced cortisol secretion, has been shown to be an important moderator of stress-related adverse consequences including increase in alcohol use [85, 86]. In addition, during the study four saliva samples are collected using Salivettes^®^ “code blue” (Sarstedt, Nümbrecht, Germany) with synthetic swabs to measure free cortisol levels and alpha-amylase activity as biological indicators of stress reactivity (Fig. 5). The first saliva sample is taken immediately before the stress induction (for detailed description for the stress induction see “Sample storage, biochemical analyses and data preparation” section). The second saliva sample is taken right after the stress induction as well as 12 (3rd salvia sample) and 24 (4th salvia sample) minutes after the stress induction. Cortisol is the final output of the hypothalamic pituitary adrenal (HPA) axis, and is among the most frequently used biological markers of psychological stress [87, 88]. Moreover, given that the biologically active (free) fraction of cortisol is reflected in saliva, it can be a preferred measure relative to serum cortisol [87, 89]. In addition, alpha-amylase is an enzyme component of saliva and has been proposed as a marker for stress-induced activity of the sympathetic nervous system (SNS). The advantage of a saliva-based measure of SNS activity is the convenience of assessing activity of both major stress systems (i.e. SNS and HPA-axis) in a single test tube, without the need for technically sophisticated instrumentation [63].

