### Statistical analyses

Main effects of stress exposure (stress vs control group) on alcohol consumption (amount of alcoholic beverage consumed) will be determined using linear regressions adjusting for the amount of non-alcoholic beverages consumed (which reduces unspecific variance in outcome). However, in case of considerable by chance differences in baseline characteristics between the two groups despite randomization, these characteristics will be included in the regression model if they are associated with alcohol consumption. To address potential biases related to missing data, we will conduct sensitivity analyses using multiple imputation.

Moderation analyses: Moderators are defined causally [50]. Linear regressions with interaction terms will be applied to test whether stress effects on alcohol consumption are moderated by childhood maltreatment, hair cortisol concentration and trait impulsivity (with main effects terms and interaction term, e.g. group × childhood maltreatment). Significant interactions indicate that a respective factor (moderator) predicts different effects of stress on alcohol assumptions. To approach causal conclusions, we will fit these models again while adjusting for shared factors of moderators and outcomes (e.g. previous stressful events, previous alcohol use) [50].

Mediation analyses: Mediators are also defined causally according to the counterfactual definition of Robins and Greenland [115] that is implemented in the ‘paramed’ package in Stata. This module allows dividing the estimated total stress effect (stress vs. control group) on alcohol consumption into a direct effect and an indirect effect mediated through stress reactivity (saliva cortisol, alpha amylase, self-reported stress), impulsivity (delay discounting), inhibitory control, and motivational sensitization (attentional bias). Mediation analyses will be adjusted for putative sociodemographic (e.g. age) and other shared factors of a potential mediator and outcome (e.g. time of day, preference of beer) as well as for the mentioned factors for moderation. The alpha level will be specified at two-sided 0.05. If necessary, the analyses will be repeated with robust standard errors (via the sandwich estimator) and robust linear regressions [116]].

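### The baseline adjustment required for the cortisol AUCs is not stated for the alpha-amylase mediator measures, so the autonomic indirect effect would be biased if pre-stress amylase is related to beer intake

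*Protocol article*

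**What the plan says.** The section on sample storage, biochemical analyses and data preparation defines AUC_G and AUC_i for cortisol and adds a modelling rule: "Analysis with these variables will be adjusted for initial cortisol concentration to alleviate confounding risk". Its reason is that "AUC variables may be comprised of variance due to stress reactivity and stress-unrelated HPA axis activity". For alpha-amylase the same paragraph lists the measures only: "With regard to alpha-amylase, both AUC measures and peak minus baseline levels will be calculated".

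The Statistical analyses section names alpha-amylase among the stress-reactivity mediators. Its covariate rule reads: "Mediation analyses will be adjusted for putative sociodemographic (e.g. age) and other shared factors of a potential mediator and outcome". The examples given are time of day and beer preference, and the factors named for moderation (earlier stressful events and alcohol use) are carried over. Initial amylase is not among them.

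A pre-stress value is available. Under Biological measures, "The first saliva sample is taken immediately before the stress induction", and both markers are measured in the same saliva samples.

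**The concern.** The AUC part of the reason given for cortisol is a property of the summary measure and applies equally to amylase. The paragraph states the safeguard for one marker and not for the other, and does not explain the difference.

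The third and fourth hypotheses name autonomic stress reactivity as a mediator, in regular and in risky drinkers. The planned mediation analysis uses a counterfactual definition, which needs common causes of mediator and outcome to be controlled. Random allocation balances initial amylase between the arms in expectation, so the effect of stress on amylase is not biased. It does nothing for the association of amylase with beer intake. If men with higher pre-stress amylase drink more (or less) beer for reasons not captured by the other covariates, a mediator that tracks the pre-stress level picks up that association. An indirect effect can then appear where there is none.

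**Working it through.** **Figures in the plan.** The article states no figure on this point, so there is none to reproduce.

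**Inputs from the article.** Sample times: "The first saliva sample is taken immediately before the stress induction"; "The second saliva sample is taken right after the stress induction as well as 12 (3rd salvia sample) and 24 (4th salvia sample) minutes". Length of the stressor: "The test is divided in three equal five-minute parts", so 3 × 5 = 15 min. Samples therefore fall at 0, 15, 27 and 39 min. The sample size is 200 per drinking stratum, and alpha is two-sided 0.05.

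**Assumed inputs (not in the article).** Equal correlation r between any two samples, 0.5 to 0.9; unit variance per sample; standardised link g between initial amylase and beer intake, 0 to 0.3; stress shifts in amylase as given below.

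**Step 1. Dependence on the pre-stress sample.** Trapezoid weights for AUC_G are 7.5, 13.5, 12 and 6 (sum 39; sum of squares 418.5). AUC_i subtracts 39 × sample 1, which gives weights -31.5, 13.5, 12 and 6 (sum 0; sum of squares 1354.5). For weights w:
- variance = (1 - r) × Σw² + r × (Σw)²
- covariance with sample 1 = w₁ + r × (w₂ + w₃ + w₄)

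At r = 0.5:
- AUC_G: variance 0.5 × 418.5 + 0.5 × 1521 = 969.75; covariance 7.5 + 0.5 × 31.5 = 23.25; correlation 23.25/√969.75 = 0.75.
- AUC_i: variance 0.5 × 1354.5 = 677.25; covariance -31.5 + 0.5 × 31.5 = -15.75; correlation -15.75/√677.25 = -0.61.
- Sample 2 minus sample 1: variance 2 × (1 - 0.5) = 1; covariance 0.5 - 1 = -0.5; correlation -0.50.

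| r | AUC_G | AUC_i | sample 2 minus baseline |
|---|---|---|---|
| 0.5 | 0.75 | -0.61 | -0.50 |
| 0.7 | 0.86 | -0.47 | -0.39 |
| 0.9 | 0.95 | -0.27 | -0.22 |

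The pre-stress sample thus accounts for 56%, 73% and 91% of the within-group variance of AUC_G at r = 0.5, 0.7 and 0.9. The change measures remove the level by subtraction but stay negatively related to it.

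**Step 2. False indirect effect with no true mediation.** It equals a × b, where a is the stress shift in the measure and b = g × covariance/variance. Assume shifts of 0.8, 0.4 and 0.2 SD in samples 2 to 4, so a = 0.8 × 13.5 + 0.4 × 12 + 0.2 × 6 = 16.8 for both AUCs. At r = 0.5 and g = 0.1:
- AUC_G: 16.8 × 0.1 × 23.25/969.75 = +0.040 SD of beer intake.
- AUC_i: 16.8 × 0.1 × (-15.75)/677.25 = -0.039 SD.

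A simulation of 1,000,000 subjects gave the same values, and -0.033 SD for peak (highest of samples 2 to 4) minus baseline. Over r = 0.5 to 0.9 and g = 0.1 to 0.3 the false effects were +0.04 to +0.13 SD for AUC_G, -0.04 to -0.12 SD for AUC_i and -0.03 to -0.11 SD for peak minus baseline. With initial amylase as covariate all three were zero within simulation error.

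**Step 3. False declaration rates at n = 200.** Assume shifts of 0.6, 0.3 and 0.3 SD and r = 0.5 to 0.7, and declare mediation when both paths reach p < 0.05. Separate simulations of 1,000 to 1,500 trials per setting agreed closely.

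| Link g | Without initial amylase |
|---|---|
| 0 | 4 to 6% |
| 0.05 | 6 to 7% |
| 0.1 | 8 to 17% |
| 0.2 | 25 to 53% (up to 55% in one run) |

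For links of 0.1 to 0.2, the ranges by measure were about 15 to 55% for AUC_G, 10 to 40% for AUC_i and 8 to 33% for peak minus baseline. With initial amylase in both models the rates were 4 to 7%.

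**Step 4. What adjustment does apart from bias.** The standard error of the AUC_G arm difference shrinks by √(1 - 0.557) = 0.67 at r = 0.5 and √(1 - 0.734) = 0.52 at r = 0.7, whatever the link with beer intake. Since AUC_i = AUC_G - 39 × sample 1, the two AUCs also give the same indirect effect once sample 1 is in both models, provided they are not transformed separately.

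**The case against.** The strongest reply is that silence is not a decision. The amylase sentence stands in a data-preparation section and says what will be calculated, not how it will be modelled. The mediation covariate rule is open-ended: if initial amylase is a common cause of mediator and beer intake, it is a shared factor in the rule's own terms, and if it is not, there is no bias. A journal article may also condense a fuller plan. This stands as far as it goes. A reader might infer that the amylase measures will be analysed unadjusted, but the article does not say so. What remains is that the article did not leave the matter to the general rule for cortisol. It wrote a specific requirement with a reason, then listed the amylase measures without it.

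Three further limits also stand.
- A reader might infer that all three measures mix reactivity with pre-stress level. That describes AUC_G only. AUC_i and peak minus baseline already subtract the initial value, and their problem is the remaining negative correlation.
- The size is assumed. The article gives no link between amylase and beer intake, no between-sample correlation and no amylase response. The link that matters is what is left after the planned covariates. The simulations contain none of these, so the rates are too high if those covariates carry part of the link.
- Requiring both paths to be significant is not a rule in the article, which specifies a counterfactual decomposition. Larger rates computed for all 400 men do not fit the third and fourth hypotheses, which are set per drinking stratum.

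**Conclusion.** The point holds as a gap in the stated adjustment with a conditional consequence. The dependence of the three amylase measures on the pre-stress sample follows from how they are built, and its size depends on the assumed correlation. Bias in the indirect effect needs a further condition that the article neither shows nor excludes: a link between pre-stress amylase and beer intake beyond the planned covariates. With no link there is no bias and no inflation. With a positive link of 0.1 to 0.2 the false effect is roughly 0.03 to 0.09 SD in absolute size, positive for AUC_G and negative for the change measures, so the planned measures could contradict each other with no true mediation. A claim that the autonomic result is necessarily biased would go beyond the documents. The change is still worth making: it removes the risk, costs almost nothing and sharpens the AUC_G arm comparison in any case.

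**What to change.** In the data-preparation section, extend the cortisol rule: every alpha-amylase mediator analysis (AUC_G, AUC_i and peak minus baseline) includes the sample-1 amylase value, transformed in the same way, as a covariate in both the mediator model and the outcome model. If the authors intend otherwise, they should say why amylase is treated differently from cortisol.

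The cost is one sentence and one degree of freedom per model, and sample 1 is already collected for this assay. Choosing a single amylase measure as the autonomic mediator is optional and not part of this point.
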